**Figure 1 F1:**
[figure not shown]
Stepped-wedge design with 12 months prerandomisation period. Pale blue cells represent inactive E-SN period, and purple cells represent active E-SN period. E-SN, electronic safety-netting.

This paper describes the protocol dated 7 October 2019 (V.1.5). Core trial information is given in table 1.

**Table 1 T1:** WHO trial registration data set

Data category	Information
Primary Registry and Trial Identifying No	ISRCTN: ISRCTN15913081
Date of Registration in Primary Registry	08/11/2019
Secondary Identifying Numbers	N/A
Source(s) of Monetary or Material Support	Cancer Research UK; Grant Codes: C48270/A27880
Primary Sponsor	University of Oxford
**Secondary Sponsor(s)**	None
Contact for Public Queries	[contact]
Contact for Scientific Queries	[contact]
Public Title	Testing an electronic safety netting system to help GPs follow-up patients with worrying symptoms
Scientific Title	CASNET2: Evaluation of an e-safety netting cancer template in primary care: a pragmatic stepped-wedge RCT
Countries of Recruitment	UK
Health Condition(s) or Problem(s) Studied	E-safety netting (E-SN) toolkit.
Intervention(s)	The researchers will recruit 60 general practices who are not currently using the E-SN toolkit, and randomise them in clusters (groups) of 10. Each cluster will have the E-SN toolkit turned on at a different time during the 12 months of the study. Once the E-SN toolkit is turned on, the GPs in the practice will be able to use it when caring for any patient they think would benefit from it, although it is expected that it will be of most use when treating patients with symptoms that might indicate cancer. The researchers will collect data from the electronic patient record system from the 12 months of the study and the 24 months before the start of the study to understand whether the introduction of the E-SN toolkit makes any difference to the diagnosis of cancer, and in particular to how quickly patients are diagnosed. The researchers will only extract records from patients who are over 18, and who have not opted out of the research.
Key Inclusion and Exclusion Criteria	GP practices will be eligible for inclusion under the following conditions: They are actively contributing to the RCGP Research and Surveillance Centre database. They use the EMIS electronic health record system. They have data available for the previous 24 months. Within the participating practices, the researchers will seek to extract data from adult patients (aged over 18 years) Exclusion criteria: GP practices who are already using the E-SN toolkit will not be eligible for the study. The researchers will not extract data from any patient under 18, or from any patient who has opted out of data sharing for research purposes.
Study type	Other
Date of First Enrolment	25/11/2019
Target Sample Size	60
Recruitment Status	Not yet recruiting
Primary Outcome(s)	Primary care interval for cancer diagnoses measured as the time between the first recorded symptom of cancer and referral to secondary cancer care, during inactive and active E-SN phases.
Key Secondary Outcomes	Proportion of cancers diagnosed after emergency presentation measured during inactive and active E-SN phases. Recorded new diagnoses in those who have a template activated, measured by cancer site and stage, and by non-cancer diagnosis, during the active E-SN stage. Total time to diagnosis measured from first recorded symptom to definitive diagnosis for all cancer diagnoses during the inactive and active E-SN phases and all diagnoses with template activation during the active E-SN phase No of GP consultations/patient between first record of symptom and cancer referral, measured during the inactive and active E-SN phase Rates of patients completing direct access cancer investigations measured during the inactive and active E-SN phase Rates of patients referred measured as 2-week wait, urgent, and routine, during the inactive and active E-SN phase Timing of template activation within the primary care interval (from first symptom to referral) measured during the active E-SN phase Template activation rate among consulting patients, both total and stratified by individual GP, measured during the active E-SN phase The proportion of diary entries completed measured during the active E-SN phase The reason for template activation measured based on 20 high-level READ codes during the active E-SN phase Symptoms leading to direct access to investigations measured during the active E-SN phase Recorded vague symptoms in the template measured during the active E-SN phase Demographic details of patients with activated templates measured during the active E-SN phase GP type completing template (eg, partner, locum, trainee) measured during the active E-SN phase Diagnostic codes in patients with activated templates measured during the active E-SN phase

EMIS, Egerton Medical Information System; E-SN, electronic safety-netting; GP, general practitioner.

The anticipated length of the study is 18 months. This consists of 3 months recruitment, followed by a 12-month period during which time the intervention will be introduced, and 3 months for analysis.

## Methods and analyses

### Outcomes and outcome definitions

#### Primary outcome: primary care interval for cancer diagnoses

The primary care interval is defined as the number of days between the first recorded symptoms of cancer (within the year prior to diagnosis) and subsequent referral for secondary cancer care.^22^ In line with published research and guidelines on diagnostic intervals, we will search the patient record for coded symptoms during the year prior to diagnosis for all patients with a cancer diagnosis: 1 year is a trade-off between misattributing unrelated symptoms occurring more than a year before and missing symptoms of relevance by restricting to a shorter period.^22 23^

#### Secondary outcomes

Full details of the secondary outcomes are given in table 2 and figure 2.

**Figure 2 F2:**
[figure not shown]
Diagram showing the definitions of time-based outcomes.

**Table 2 T2:** Outcomes, measures and time periods of measurement for primary and secondary outcomes

Outcome	Measure	Inactive study period	Active study period	Template activations only
Primary outcome				
Primary care interval for cancer diagnoses	Measured as the no of days between first recorded symptoms of cancer (within the year prior to diagnosis) and subsequent referral for secondary cancer care	X	X	
Secondary outcomes				
Proportion of cancers diagnosed after emergency presentation	Proportion of cancers for which diagnosis is made prior to referral, including following A&E or inpatient episodes. Where there is uncertainty regarding the route of diagnosis, the RCGP RSC network will contact the practice in an attempt to augment the data. Algorithms will also be developed to identify emergency presentations of cancer.	X	X	
Recorded new diagnoses in those who have a template activated	By cancer site and stage, and non-cancer diagnoses. Coded entries for all alternative diagnoses where the E-SN toolkit has been activated will be identified.		X	X
Total time to diagnosis (from first recorded symptom to definitive diagnosis)	Measured from first recorded symptom of cancer (within the previous year) to definitive diagnosis for all cancers diagnosed, and for all patients with an activated template	X	X	X (for non-cancer diagnoses)
No of GP consultations/patient between first record of symptom and cancer referral	Measured as no of primary care consultations between the first recorded symptoms (within the year prior to diagnosis) and subsequent referral, per patient.	X	X	
Rates of patients completing direct access cancer investigations	Measured as the no of patients undergoing direct access cancer investigations (according to those specified in referral guidelines NG12) in each period divided by the person years of observation for that period.	X	X	
Rates of patients referred for cancer	Referrals rates via 2-week wait, urgent, and routine routes for all patients referred for specialist opinion to a secondary care cancer specialist	X	X	
Timing of template activation	Measured as the no of days between first recorded symptoms (within the year prior to diagnosis), and template activation and the no of days between template activation and subsequent referral.		X	X
Template activation rate among consulting patients	Measured as the number of patients with an activated template divided by the no of patients consulting, in each time period. Both total rate and rate stratified by individual GP will be measured.		X	X
Proportion of diary entries that were completed	Measured as the no of diary entries that were completed divided by the number of diary entries that were opened.		X	X
Reason for template activation	The coded reasons for activating the template, Based on 20 high level READ codes		X	X
Symptoms leading to direct access to investigation	All symptoms recorded in patients undergoing direct access cancer investigations	X	X	
Recorded vague symptoms in the template	All symptoms recorded within the template.		X	X
Demographic details of patients with activated templates	Age and sex of patients that had a template activated during the course of the trial.		X	X
GP type completing templates	Descriptive data on the type of GP that first activated the template (eg, partner, locum, trainee)		X	X
Diagnostic codes in patients with activated templates	Diagnoses recorded after the activation of template.		X	X

E-SN, electronic safety-netting; GP, general practitioner; RSC, Research and Surveillance Centre; RSC, Research and Surveillance Centre.

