### Intervention

The intervention consists of activation and the implementation of the E-SN toolkit at participating practices. All practices will receive training in the use of the E-SN toolkit from RCGP PSC PLOs prior to their switching date. Clinicians will be able to use the E-SN templates at their own discretion during the active period, with no requirements on which patients should or should not receive safety netting. Clinical care of patients will continue as normal throughout the study.

The E-SN toolkit uses a templates to track cancer events like referrals, direct access tests and monitoring of low risk through read codes attached to diary entries. Expired diary entries would be identified using automated searches and actioned by the administration lead as appropriate. If an event was complete, for example, normal scan results done in 2 weeks and result back—then the diary entry is closed, resolving the episode. The E-SN toolkit has extra features such as popup alerts to remind any user there is an open diary entry and also allows the E-SN toolkit to popup automatically if a relevant code is used in the clinical records.

Further details and demonstration video are available from: https://www.uclh.nhs.uk/OurServices/ServiceA-Z/Cancer/NCV/MICa/Pages/Primarycareimprovement.aspx

Practices will all be encouraged to adhere to the schedule for switching and will receive part-payment for study initiation and then full payment when they adhere to the activation schedule.

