### Data management

The principal data source for the this study are pseudonymised routinely collected care data extracted from general practices of the RCGP RSC network’s database; there are over 500 general practices in this network. All general practices in the UK use an EHR to maintain patient medical records. Data are entered into a patient’s computerised medical system as coded data or free text. The RCGP RSC extract only coded data, that is, where the clinician codes a disease or symptom into their EHR system.^27^

The RCGP RSC has no role in updating clinical data recorded by clinicians as part of their consultation and care. However, the RCGP RSC practices do received focused feedback about data quality around its surveillance function, influenza other infections, vaccine update and effectiveness. This is done via team of PLOs and a dashboard.^28 29^

RCGP RSC maintains an auditable trail for all the stages of data processing to ensure the quality of data are not compromised by the processing. For example, checking the prevalence of certain conditions and outliers revealed by the data is consistent with those reported in the literature. The standard operating procedures for data extraction and data processing, and data access are available from https://clininf.eu/index.php/information-governance/

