### Statistical analysis

In patients with a diagnosis of cancer, we will calculate the primary outcome of primary care interval (time between first recorded symptom and referral), proportion diagnosed after emergency presentation and the recorded diagnosis. Among consulting patients, we will calculate the rate of direct access cancer investigation and rates of referrals via 2 weeks wait, urgent and routine pathways, as well as the number of consultations during the primary care interval, and the template activation rate. A patient referred to: a 2-week wait pathway will be reviewed by a specialist within 2 weeks; an urgent pathway will be reviewed as a priority but the exact timing varies between specialty and healthcare setting; a routine pathway requires specialist review but on a non-urgent basis.

Regarding the analysis of the stepped-wedge design and the effect of correlation of observations within clusters, will model the association using a fixed effect for the intervention condition of the cluster at each time step, a fixed effect for time and other covariates (eg, changes in cancer guidelines), and then include a random effect for practice and a random effect for patient to account for correlation of the observations from the same centre and from the same participant.

Analyses will include all patients registered at participating practices. Practices that withdraw their agreement to participate will be included in analyses up to the point of withdrawal, unless they indicate that they wish to withdraw previously collected data from analysis.

Our primary analysis will be carried out on an intention to treat principle. Therefore, if any practice does not switch on the E-SN toolkit at the correct time for their cluster, we will carry out the analysis under the assumption that the E-SN toolkit was switched on at the correct time.

The primary care interval is defined from the presence of symptoms and referral in the primary care record. Symptoms of interest will include all symptoms included in the urgent referral guidelines including vague symptoms such as weight loss, tiredness and back pain.^35 36^ Missing data for these variables in the record will be interpreted as the absence of symptoms or referral, respectively. Extracted data from the primary care record will be limited to the study period plus the preceding year, so symptoms recorded prior to this will not be visible to the research team.

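### Emergency presentation is defined by the lack of a prior referral, and uncoded referrals read as absent, so a phase difference in referral coding can bias this secondary outcome

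*Protocol article*

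**What the plan says.** Four statements in the protocol article bear on this outcome.

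- **Definition (Table 2):** "Proportion of cancers for which diagnosis is made prior to referral". The cell then names A&E and inpatient episodes; these are examples within the definition and do not limit it.
- **Data source (Data management):** "The RCGP RSC extract only coded data, that is, where the clinician codes a disease or symptom into their EHR system". Free text is not seen.
- **Missing referral (Statistical analysis):** "Missing data for these variables in the record will be interpreted as the absence of symptoms or referral, respectively". The sentence stands in the paragraph on the primary care interval.
- **Intervention:** the toolkit uses templates to "track cancer events like referrals, direct access tests and monitoring of low risk through read codes attached to diary entries". Practices already deploying it are excluded, so this coding route exists only in the active phase.

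The same Table 2 cell adds two safeguards. The first is a query: "Where there is uncertainty regarding the route of diagnosis, the RCGP RSC network will contact the practice in an attempt to augment the data". The second is that algorithms to identify emergency presentations will be developed. The Randomisation and blinding section keeps extraction staff blind to the allocated order and keeps data management blind to switch timing; clinicians and practice managers know their phase.

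The Sample size section puts the current emergency share at about 19% and states power to detect a difference of 5% with nine cancers per step per cluster.

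**The concern.** The operative test is that no referral precedes the diagnosis. It is not evidence that an emergency occurred. Two kinds of cancer can therefore be counted wrongly: those referred without a code, and those diagnosed without referral by a route that was not an emergency.

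A constant error would mainly shift the level. The difficulty is that the intervention touches the variable used for classification. If activating the toolkit changes how often referrals are coded, the error changes at the switch date in each practice. It then coincides with the exposure, and neither randomisation of the switch date nor the fixed effect for time removes it. A fall in measured emergency presentations could then be a coding artefact, with no patient diagnosed differently. This is the only secondary outcome for which the article gives a detectable difference.

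**Working it through.** **1. Reproduce the plan's figure.** Inputs from the Sample size section and Figure 1 legend: 60 practices in six blocks of 10, nine cancers per practice per two-month step, a 12-month preintervention period (six steps), then six rollout steps; 19% against 14%. Assumed: two-sided alpha 0.05, 80% power (stated only for the primary outcome), intracluster correlation (ICC) 0 to 0.10. Method: Hussey–Hughes variance with fixed period effects and a random practice effect; detectable difference = (1.96 + 0.84) × SE.

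| Variance taken at | Detectable difference over ICC 0–0.10 |
|---|---|
| average of 19% and 14% (16.5%) | 4.5 to 5.0 points |
| 19% | 4.8 to 5.3 points |

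The stated 5 points reproduces.

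**2. Misclassification from uncoded referrals.** Let e be the true emergency share and u the share of referred cancers with no coded referral. Take every other cancer as referred.

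- Observed share = e + (1 − e) × u
- Spurious change between phases = (1 − e) × (u inactive − u active)

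With e = 0.19, the multiplier is 0.81. The documents do not give u, so these values are assumptions:

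| u inactive → u active | Observed share | Spurious fall |
|---|---|---|
| 5% → 2% | 23.1% → 20.6% | 2.4 points |
| 10% → 5% | 27.1% → 23.1% | 4.1 points |
| 15% → 5% | 31.2% → 23.1% | 8.1 points |

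To match the detectable difference, u must fall by 0.05 / 0.81 = 6.2 points, which is possible only if at least 6.2% of referrals are uncoded at baseline. If the 19% already contains uncoded referrals, then for u = 10% the true share is 1 − 0.81/0.90 = 10%, and the 10% → 5% case gives 0.90 × 0.05 = 4.5 points.

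**3. Effect of practice queries.** If queries correct a fraction r of the uncoded referrals, the fall is multiplied by (1 − r). For 10% → 5%: r = 0.5 leaves 2.0 points; r = 0.9 leaves 0.4 points.

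**4. Chance of a false positive.** At ICC 0.02 with variance at 19%, SE = 0.0186. A spurious 4.05-point fall is declared significant with probability Φ(0.0405/0.0186 − 1.96), about 58%. If the variance is taken at the inflated share of 27.1%, SE = 0.0186 × √(0.271 × 0.729 / (0.19 × 0.81)) = 0.0211, and the probability is about 48%. For a 2-point fall it is about 19% (variance at 19%).

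**5. Direction.** Let d be the share diagnosed before referral by a non-emergency route. Observed share = e + d + (1 − e − d) × u. In the 10% → 5% case with d = 0 before activation, the active-phase share becomes 23.05% + 0.95 × d. A rise in d of 4.05 / 0.95 = 4.3 points cancels the spurious fall, and a larger one reverses it.

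**The case against.** The strongest reply is that Table 2 already provides for this. It plans practice queries and an emergency-presentation algorithm, and details of both may properly sit in the full protocol or analysis plan. The missing-referral rule is written for the primary care interval, so the outcome-specific text could be taken to govern here. Data handling is blind to switch timing. No section says that referral coding will improve, how often referrals are uncoded, or that a diary-entry code is the referral code extracted; use of the templates is at the clinician's discretion.

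Much of this stands as a limit on size and certainty. It does not remove the point. The emergency definition uses the same referral variable as the interval, and nothing exempts it from the rule. A missing referral already read as no referral need not register as uncertain, so it need not trigger a query. Those who answer a query know their phase. Nothing says that the algorithm replaces the stated definition.

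A reader might infer three stronger conclusions that the documents do not support:

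- *That the toolkit will produce a spurious fall.* Better referral coding is plausible from the Intervention section but is not stated or quantified.
- *That the bias always favours the toolkit.* The toolkit also tracks direct-access tests, and more diagnoses by that route before referral would push the measured share up.
- *That screening-detected cancers add to the phase difference.* They have no stated link to phase; they raise the level above the 19% planning figure.

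**Conclusion.** The point holds as a risk of bias in one secondary outcome. Followed as written, the definition and the missing-referral rule can count uncoded referrals and non-emergency unreferred routes as emergency presentations, and the share so counted can change with the phase.

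The multiplier of 0.81 follows from the protocol's 19%. The size then depends on an assumed change in the uncoded share: about 2 to 8 points over the cases shown, and about 4 points for 10% to 5%, before queries. Effective queries could make it small. The net direction is not certain. The primary outcome is not at issue here. The consequence is that a significant change in this outcome, in either direction, could not be told apart from a change in coding or in the route to diagnosis.

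**What to change.** Before outcome extraction:

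1. Use the algorithm already planned to classify emergency presentation on positive coded evidence: an A&E attendance or unplanned admission before diagnosis, within a window fixed in advance.
2. Keep two further categories separate: other route (such as screening or a direct-access test) and route unknown (no coded referral). Do not apply the missing-means-absent rule to this outcome.
3. Send practice queries by the same written rule in both phases, with those who select the cases blind to phase.
4. Report unknown route and completeness of referral coding by phase, with bounds that count the unknowns as all emergency and as none.

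The cost is small: one definition changes, and neither design nor recruitment is affected. The Data extraction section does not name A&E or admission codes, so the sponsor should confirm that the extract holds them; the planned algorithm appears to need them in any case. Some cancers will move to unknown and precision falls slightly. The bounds may be wide: with 10% of referrals uncoded and every true emergency coded, they run from 19% to 27.1% in the inactive phase. That width shows how much the present definition leaves to coding.

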### Randomisation and blinding

The eligible practices will be ranked according to their list size from smallest to the largest by the RCGP RSC. These will then be stratified into 10 strata (by list size) such that each strata contains the same number of practices. This is based on the allocation of 10 practices per step. Practices will be randomised in blocks of 10 to the timing of activation of the E-SN toolkit and will crossover in these blocks to the activated phase every 2 months. Therefore, practices will contribute between 2 months and 12 months of E-SN toolkit-activated time (figure 1).

A statistician ([name], Nuffield Department of Primary Care Health Sciences, University of Oxford) who is independent to the intervention development and implementation will produce a stratified randomisation schedule so that within each strata, practices are randomly allocated to each of the six steps, with some replacement practices. The random sequence will be generated using R software. The allocation will be undertaken for all practices at the same time. Where replacement practices are required, these will be taken from the same strata where possible. If no replacement practices from the same strata are available a coin toss will determine whether the next highest or lowest strata will be used to provide replacement practices.

Given the practice change nature of the intervention, clinicians and practice managers will be aware when their practice has switched to the intervention period. Consulting patients providing outcome data will not be informed of the experimental nature of the E-SN toolkit activation and therefore will be blind to the stage of study occurring in the practice they attended. Study personnel involved in extracting outcome data will be blind to the allocated order of the delivery of the intervention across the practices. All data management of extracted data to calculate the outcome measures will be conducted blinded to the timing of switching to intervention. Similar methods have been used in other implementation SW-CRCTs.^26^

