### Data extraction

Data extractions from all participating practices will correspond to two major time points: at the start of the introduction to the stepped wedge implementation of the E-SN toolkit, and at the end of the stepped wedge period (12 months later). At these two time points, consultation data from the participating practices will be obtained for the previous 24 months. Data from the previous 24 months are required to identify cancers detected in 12 months prior to start, plus the first recorded symptom of cancer during the primary care interval, allowing for this interval to cover up to a year prior to diagnosis.

Records from all patients who are adults aged 18 years and above, registered at participating practices and who have not opted out of sharing data for research purposes will be extracted. Pseudonymised patient information will include: demographic information of age, sex, dates of clinical consultations; coded consultation data for symptoms, diagnoses, tests ordered and referrals made within the consultation records. Where a definitive diagnosis has been made (for cancer and non-cancer conditions), the clinical features recorded in the year prior to diagnosis will be captured. These actions will be achieved by extraction of the EHR rather than by hand searching notes.

Practices will be asked to search for open diary entries every week during the intervention period, and to download and save these to an Excel spreadsheet (locally). The central study research team will use these spreadsheets to track which diary entries are closed during the course of the intervention.

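### Emergency presentation, compared between phases, is supplemented by replies from practices that know their phase; the blinding assurances do not cover these replies

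*Protocol article*

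**What the plan says.** Table 2 lists emergency presentation as a secondary outcome measured in both the inactive and the active period. Its measure is: "Proportion of cancers for which diagnosis is made prior to referral, including following A&E or inpatient episodes". Two further sentences say how the route is established. One is the practice query: "Where there is uncertainty regarding the route of diagnosis, the RCGP RSC network will contact the practice in an attempt to augment the data". The other is: "Algorithms will also be developed to identify emergency presentations of cancer". The row gives no order of precedence between the two.

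The section on randomisation and blinding makes three relevant statements:
- At practices, "clinicians and practice managers will be aware when their practice has switched to the intervention period".
- For extraction, "Study personnel involved in extracting outcome data will be blind to the allocated order of the delivery of the intervention across the practices".
- For derivation, "All data management of extracted data to calculate the outcome measures will be conducted blinded to the timing of switching to intervention".

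The Intervention section has liaison officers of the surveillance network train each practice before its switching date. Data extraction describes capture from the electronic record and has practices search for and save open diary entries every week during the intervention period. Sample size gives a baseline of about 19% emergency presentations and a detectable difference of 5% with nine cancers per step per cluster.

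**The concern.** A reader of the blinding paragraph would conclude that every outcome is derived from extracted records by people who do not know when a practice switched. For this outcome that is not the whole story. Some cancers may be classified with help from the practice, and the practice knows whether it was using the toolkit when the cancer was diagnosed.

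Replies need not be given in bad faith to differ by phase. The outcome turns on whether diagnosis came before referral. In the active phase a practice may have diary entries and saved weekly lists that track referrals and tests; in the inactive phase it has none from the toolkit. So the ability to answer, and possibly which cases look uncertain at all, could follow activation status. This mechanism is an inference; the documents do not state it.

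The planned model has fixed effects for time and a random effect for practice. These do not remove a difference that follows activation within a practice, because that is exactly the contrast the intervention effect estimates. What is at stake is whether an apparent effect on emergency presentation, in either direction, could be explained by how uncertain cases were resolved.

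**Working it through.** **1. The passages side by side**

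| Step in forming the outcome | Who supplies it | Covered by a blinding statement? |
|---|---|---|
| Extraction of coded data | Study personnel | Yes, blind to allocated order |
| Derivation from extracted data | Data management | Yes, blind to switch timing |
| Algorithm for emergency presentation | Derived from data | Yes, if run on extracted data |
| Reply on an uncertain route | The practice | No; practices are declared aware |

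The last row lies outside the two assurances. Masking the person who sends the query would not make the practice blind.

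**2. The plan's own figure, for scale**

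Inputs from Sample size: 60 practices, six steps of 10, nine cancers per practice per two-month step, a 12-month pre-intervention period (taken as six two-month periods) and a 19% baseline. Assumptions not in the article for this outcome: two-sided alpha 0.05, 80% power (stated for the primary outcome only), the 5% read as percentage points, and an intracluster correlation (ICC) of 0 to 0.10.

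The Hussey-Hughes variance is

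Var = I·s·(s + T·τ²) / [(I·U − W)·s + (U² + I·T·U − T·W − I·V)·τ²]

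with s = p(1 − p)/9 and τ² = p(1 − p)·ICC/(1 − ICC). For this design I = 60, T = 12, U = 210, W = 9100 and V = 910, so I·U − W = 3500 and the bracket multiplying τ² is 31,500.

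The detectable difference is (1.96 + 0.84)·SE, with p the mean of the two proportions:
- 19% against 14%: 4.5 points (ICC 0) to 5.2 points (ICC 0.10).
- 19% against 24%: 5.0 to 5.7 points.

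The stated 5% is therefore plausible, at least for a decrease. It cannot be strictly reproduced, because ICC, alpha and power for this outcome are not given.

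**3. Illustrative bias**

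Let u be the share of cancers queried (taken as equal in both phases) and d the difference between phases, due to reporting alone, in the share of queried cancers counted as emergency. Then bias = u × d. **The documents give neither u nor d.**

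| u | d = 0 | d = 20 points |
|---|---|---|
| 5% | 0 | 0.05 × 20 = 1 point |
| 10% | 0 | 0.10 × 20 = 2 points |
| 20% | 0 | 0.20 × 20 = 4 points |

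**4. What such a bias would do to the test**

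Under a true null, p = 0.19 and p(1 − p) = 0.1539, so s = 0.0171.
- ICC 0.01: τ² = 0.001555. Var = 60 × 0.0171 × 0.03576 / (59.85 + 48.97) = 0.000337, so SE = 1.84 points.
- ICC 0.05: τ² = 0.0081. Var = 60 × 0.0171 × 0.1143 / (59.85 + 255.15) = 0.000372, so SE = 1.93 points.

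Rejection probability = 1 − Φ(1.96 − b/SE) + Φ(−1.96 − b/SE):

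| Bias b | ICC 0.01 | ICC 0.05 |
|---|---|---|
| 0 | 5.0% | 5.0% |
| 1 point | 8.5% | 8.1% |
| 2 points | 19.3% | 17.9% |
| 4 points | 58.7% | 54.5% |

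These rates are conditional on the assumed u and d. They show how sensitive the test would be. They are not an estimate of what will happen.

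**The case against.** The strongest case against the point runs as follows.

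- **No rule is broken.** The blinding statements bind extraction personnel and the handling of extracted data, and the same paragraph openly says that practices are aware. This stands. A reader might infer a contradiction; the text supports only a tension. The remark that data come "These actions will be achieved by extraction of the EHR rather than by hand searching notes" in effect concerns the coded items and clinical features described just before it, so it does not rule out the query either. (The sentence reads in full: "These actions will be achieved by extraction of the EHR rather than by hand searching notes".)
- **Replies augment and do not adjudicate.** This stands. Table 2 describes an attempt to add data, alongside algorithms, and does not say that a reply overrides the record.
- **This is not the trial's only harm signal.** This stands. With no monitoring committee and no formal monitoring of serious adverse events, a reader might see it that way. But the protocol does not label it a harm outcome, and total time to diagnosis and the primary care interval would also show missed follow-up.
- **Route is fairly factual, and differential error is not shown.** This stands as a limit on size. Template use is discretionary, and the article does not say that liaison officers send the queries. If queries follow the two planned extractions (their timing is not stated), those for the trial year would go out after every practice had switched, so the act of contact would not track phase within that year. The practice would still know on which side of its switch each cancer fell.
- **Operational detail belongs in the full protocol or analysis plan.** This stands for who sends the query and how it is worded. It does not dispose of the point, because using replies from unblinded practices is a method the article states.
- **Coded data may also depend on phase.** This stands. Template codes exist only in the active phase, so a coded-only analysis cannot be presumed free of bias.

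**Conclusion.** The concern holds in a limited form. A secondary outcome that is compared between phases, and has its own power statement, is supplemented by replies from a source the protocol declares unblinded. The blinding assurances do not reach those replies, and the article states no precedence between a reply and the algorithm.

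Neither the size nor the direction of any bias follows from the documents. The 1 to 4 points in the illustration rest wholly on the assumed 5% to 20% queried and the assumed 20-point difference in replies; with no difference in replies the bias is zero. A reader might go further and conclude that the bias could match the whole detectable difference. That needs inputs the documents do not supply. The primary outcome is not affected, since Table 2 describes no practice query for it. This is a worthwhile, inexpensive improvement and not a fundamental flaw.

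**What to change.** In the emergency presentation row of Table 2, state that:
1. the planned algorithm is applied identically to coded data in both phases before any query is made;
2. uncertain cases are flagged and queried by staff without the activation schedule, using one fixed closed question on the date and route of the episode;
3. the outcome is reported both on coded data alone and with practice replies added, with the numbers queried and reclassified shown by phase.

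A sentence in the section on randomisation and blinding should acknowledge that practice replies are an unblinded input to this outcome.

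The cost is a change of wording, a masked route for sending queries and one additional analysis; no new kind of data is needed. The downside is that some routes stay less well classified in the coded-only analysis, which may itself carry phase-dependent coding. Both analyses should therefore be shown and neither assumed unbiased. If they agree, the effect does not depend on the replies; if they differ, the counts by phase show where the difference arises.
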